#### ICBT Without Guidance

In this condition, participants will also have access to SOLUS-D. However, they will not be guided and will use it on their own; yet, the participants will receive weekly automated and fully standardized emails during the 10 weeks. The content of these emails aims to remind and motivate participants to continue engaging with the program. Within the information about group allocation, it is explicitly stated that the automated email is automatically sent from a computer and not by a human being. During the intervention period, questions concerning technical issues with the program will be answered upon request by the study team.

#### Wait-list Control Group

Participants in this condition will receive access to the unguided intervention 10 weeks after randomization (ie, after the postassessment time point).

### Measures

#### Overview

Demographic information such as gender, marital status, and education level will be self-reported by participants at baseline. In addition, we will assess participants’ medication status at baseline and their use of psychotherapy at every measurement time point. Table 2 summarizes the instruments and schedule of the assessments in this study. In case there was no German version of a scale available, the original scale was translated from English to German by our research group and back translated by a native English-speaking person. Differences between this back-translation and the original scale were discussed until a consensus was reached regarding the necessary changes in the German version.

**Table 2 table2:** Assessment timeline.

Type of variable and variable		Measurement	Baseline (time point 0)	5 weeks (time point 1)	10 weeks (time point 2)	6 months^a^ (time point 3)	12 months^a^ (time point 4)
**Primary outcome**							
	Loneliness	UCLA^b^ Loneliness Scale 9-item version	✓	✓	✓	✓	✓
**Secondary outcomes**							
	Depression	Patient Health Questionnaire-9	✓	✓	✓	✓	✓
	Social anxiety	Social Interaction Anxiety Scale and Social Phobia Scale	✓	✓	✓	✓	✓
	Satisfaction with life	Satisfaction with Life Scale	✓	✓	✓	✓	✓
	Social isolation	Social Network Index	✓		✓	✓	✓
	Self-compassion	Sussex Oxford Compassion Scale for the Self	✓		✓		
	Maladaptive personality traits	PID-5-BF+^c^	✓		✓		
	Misantropy	Bern Embitterment Inventory^d^	✓		✓		
	Motivation for solitude	Motivation for Solitude Scale–Short Form^d^	✓		✓		
	Negative effects	Inventory for the Assessment of Negative Effects of Psychotherapy^a^			✓		
	Patient satisfaction	Client Satisfaction Questionnaire^a^			✓	✓	
	System usability	System Usability Scale^a^			✓		
	Mental disorders	Mini Diagnostic Interview for Mental Disorders	✓			✓^a^	
**Mechanisms of change**							
	Interpretation bias	Interpretation and Judgmental Bias Questionnaire^e^	✓	✓	✓		
	Rejection sensitivity	Adult Rejection Sensitivity Questionnaire	✓	✓	✓		
	Social avoidance	Cognitive-Behavioral Avoidance Scale^d^	✓	✓	✓		
	Self-Disclosure	Distress Disclosure Index	✓	✓	✓		
	Authenticity	Kernis and Goldman Authenticity Inventory–Short Form	✓	✓	✓		
	Self-esteem	Rosenberg Self-Esteem Scale	✓	✓	✓		
	Therapeutic alliance	Working Alliance Inventory for internet interventions^a,f^		✓			
**Moderators**							
	Mobility	Patient Questionnaire for Medical Rehabilitation^d^	✓				
	Attachment style	Adult Attachment Scale	✓				
	Childhood trauma	Childhood Trauma Questionnaire	✓				
	Demographic variables	N/A^g^	✓				

^a^Intervention groups only.

^b^UCLA: University of California, Los Angeles.

^c^PID-5-BF+: Personality Inventory for the Diagnostic and Statistical Manual of Mental Disorders-5 Brief Form Plus.

^d^Only subscales.

^e^Interpretation bias only.

^f^A total of 4 items will not be presented to participants in the SOLUS-D+automated feedback group as they are not plausible (eg, “The coach really cares about my well-being”).

^g^N/A: not applicable.

#### Primary Outcome Measure

Loneliness, assessed with the 9-item short version [66] of the Revised UCLA Loneliness Scale [67,68] at the postassessment time point, is the primary outcome. The original scale, comprising 20 items, assesses 3 different facets of loneliness: intimate loneliness, relational loneliness, and collective loneliness [69]. The short version comprises the 3 items with the highest loading on each factor [70]. The reliability and validity of this short version are comparable with those of the full 20-item version [70]. The response options are *never* (1), *rarely* (2), *sometimes* (3), and *always* (4). Ratings are summed, and scores range from 9 to 36, with higher scores indicating greater loneliness levels.

Previous studies revealed a discrepancy, for example, in the prevalence of loneliness, when assessing loneliness directly or indirectly [71]. Therefore, loneliness will be further assessed with a single direct question (“Do you feel lonely”; rated on a 4-point scale with the response options 0=*no, never;* 1=*yes, sometimes*; 2=*yes, quite often*; 3=*yes, very often*) and a 3-item very short version [72] of the UCLA Loneliness Scale for which German population norms exist [73].

#### Secondary Outcome Measures

*Depressive symptoms* will be assessed using the 9-item depression module of the PHQ-9 [74,75]. All 9 items correspond to the 9 Diagnostic and Statistical Manual of Mental Disorders (DSM)–IV criteria for depression. The items are rated on a 4-point scale from 0 (not at all) to 3 (nearly every day). Ratings are summed up, and scores range from 0 to 27. The PHQ-9 shows good validity [74] and sensitivity to change [75].

*Symptoms of social anxiety* will be assessed with the short forms of the Social Interaction Anxiety Scale and Social Phobia Scale [76]. These 2 scales complement each other and are mostly administered together. The 12 items are rated on a 5-point scale from 0 (not at all) to 4 (extremely). The Social Interaction Anxiety Scale and Social Phobia Scale showed good validity and sensitivity to change over time [76].

*Satisfaction with life* will be measured with the Satisfaction With Life Scale [77,78]. A total of 5 items, such as “In most ways my life is close to my ideal,” are rated on a 7-point scale from 1 (strongly disagree) to 7 (strongly agree). This scale shows good psychometric properties and norm values based on a large German sample [79].

*Self-esteem* will be assessed using the 10-item revised German version [80] of the Rosenberg Self-Esteem Scale [81]. This scale measures positive and negative aspects of self-esteem. Items are rated on a 4-point Likert scale ranging from 0 (strongly agree) to 3 (strongly disagree). The internal consistency of the 1 factorial solution is good (Cronbach α=.84) [80].

*Objective social isolation* will be measured using the Social Network Index [82]. This scale comprises 12 items assessing 12 different types of social relationships (eg, partner, parents, children, other close family members, close neighbors, friends, and fellow volunteers). Participants will be asked how many relationships of each type they have and how many of them they are in contact with at least once every 2 weeks. The network size, network diversity, and number of embedded subnetworks can be calculated using the Social Network Index [83].

*Maladaptive personality traits* will be assessed using the 34-item Personality Inventory for the DSM-5 Brief Form Plus [84], a 34-item short version of the Personality Inventory for DSM-5 [85]. The Personality Inventory for DSM-5 Brief Form Plus assesses 5 domains and 15 facets according to criterion B of the Alternative Model of Personality Disorders included in DSM-5, which are Negative Affectivity, Detachment, Antagonism, Disinhibition, and Psychoticism, plus the International Classification of Diseases (ICD)-11 domain Anankastia comprising 2 facets. Items are rated on a 4-point response scale ranging from 0 (very false or often false) to 3 (very true or often true). Scores can be calculated for the 17 facets and the 6 domains. Good internal consistency has been shown for the domain trait scores (McDonald ω=0.81) [84]. The average score of these 6 maladaptive trait domains can be used as an indicator of the severity of personality dysfunction according to the DSM-5 section III and the ICD-11 classification of Personality Disorders [86].

*The negative effects of the intervention* will be assessed with the Inventory for the Assessment of Negative Effects of Psychotherapy (INEP) [87]. The INEP assesses any adverse effects on social, intrapersonal, or work-related situations and whether they are attributed to the intervention. As in other studies on internet-based interventions, the INEP was slightly adapted for its use with internet-based interventions.

*Client satisfaction with the treatment* will be assessed with the Client Satisfaction Questionnaire-8 [88]. The 8 items are rated on a 4-point scale from 1 (low satisfaction) to 4 (high satisfaction). We adapted this measure to explore participants’ satisfaction with the internet intervention applied in this study. The Client Satisfaction Questionnaire-8 is a valid measure for assessing client satisfaction [88] and shows good internal consistency (Cronbach α=.90) [89].

*The usability* of the web-based program will be assessed using the System Usability Scale [90]. For this study, we adapted the measure to explore the experienced usability of the web-based program used in this trial. A total of 10 items are rated on a 5-point scale ranging from 0 (*strongly disagree*) to 4 (strongly agree). The usability score is obtained by multiplying the sum of all item scores by 2.5 and ranges from 0 to 100.

*Diagnoses of mental disorders* will be assessed using the short version of the Mini-DIPS–Open Access [91]. This structured interview is openly accessible and allows the reliable assessment of diagnoses according to the DSM-5 and ICD-10.

*Adherence* to the web-based program will be assessed using different indicators, such as (1) the number of modules completed and (2) time spent in the program. A module is completed when each page per module has been clicked at least once.

#### Assessment of Potential Mechanisms of Change

*Interpretation bias* will be assessed using the corresponding subscale of the Interpretation and Judgmental Bias Questionnaire [92,93]. The Interpretation and Judgmental Bias Questionnaire is a 24-item scale comprising brief scripts of 20 social events and 4 nonsocial control events. The social events can be divided into ambiguous, mildly negative, profoundly negative, and positive social events. For this study, we only assessed interpretation and not judgmental bias. For this purpose, each script will be followed with 4 alternative answers. The answers reflect positive, neutral, mildly negative, or profoundly negative interpretations of the event. The participants will be asked to rank the probability of these 4 interpretations. The score is the mean rank given to the profoundly negative interpretation of the scenarios and ranges between 1 and 4. A lower score indicates more negatively biased processing [94].

*Rejection sensitivity* will be assessed using the adapted adult version (Adult Rejection Sensitivity Questionnaire) [95] of the Rejection Sensitivity Questionnaire [96]. In the Adult Rejection Sensitivity Questionnaire, 9 hypothetical interpersonal situations are presented, and respondents indicate how they would feel or think in the stated situations. Respondents indicate on a 6-point scale how concerned they would be in that situation (very unconcerned to very concerned) and how likely they would expect to be accepted (very unlikely to very likely). One study shows high internal consistency (Cronbach α=.87) for the total score in a sample of adults with borderline personality disorder and acceptable consistency (Cronbach α=.75) for a healthy sample of adults [97].

*Social avoidance behavior* will be assessed with the subscale Behavior-social avoidance of the Cognitive-Behavioral Avoidance Scale [98,99]. Participants are asked to rate their social behavior on a 5-point Likert scale ranging from 1 (not at all true for me) to 5 (extremely true for me; eg, “I make excuses to get out of social activities.”). The subscale has shown good internal consistency (Cronbach α=.86) [99].

*Comfort with self-disclosure* will be assessed using the Distress Disclosure Index [100]. It is a 12-item scale designed to measure the degree to which a person is comfortable talking with others about personally distressing information (eg, “I am willing to tell others my distressing thoughts”). Items are rated on a 5-point Likert-type scale, with responses ranging from 1 (strongly disagree) to 5 (strongly agree). The Distress Disclosure Index has shown good psychometric properties [101].

*Authenticity* will be assessed using the 20-item short form (Kernis-Goldman Authenticity Inventory [KGAI]–Short Form [102]) of the KGAI version 3 [103]. It assesses 4 underlying dimensions of authenticity (awareness, unbiased processing, behavior, and relational orientation), and items are rated on a 5-point Likert scale ranging from 1 (*strongly disagree*) to 5 (*strongly agree*). The KGAI–Short Form shows good internal consistency (Cronbach α=.87) and good convergent and discriminant validity [102].

*Self-compassion* will be assessed using the Sussex Oxford Compassion Scale for the Self [104]. This scale measures five dimensions of compassion: (1) recognizing suffering, (2) understanding the universality of suffering, (3) feeling for the person in suffering, (4) tolerating uncomfortable feelings, and (5) motivation to act to alleviate the suffering. The 20 items will be rated on a 5-point scale ranging from 1 (not at all true) to 5 (always true). This scale shows adequate internal consistency and convergent and discriminant validity [104].

*Misanthropy* will be assessed using the respective subscale of the Bern Embitterment Inventory [105]. This subscale measures a general contempt of human beings (eg, “Sometimes I feel hatred towards mankind or a part of it”). The 4 items are rated on a scale from 0 (I do not agree) to 4 (I agree). The Cronbach α for this scale is .65 [105].

*Self-determined motivation for solitude* will be assessed with the corresponding 8-item subscale from the Motivation for Solitude Scale–Short Form [106]. This subscale measures the degree of the desire to spend time alone. Items are introduced with “When I spend time alone, I do so because...” and rated on a 4-point Likert scale from 1 (not at all important) to 4 (very important). The answers are summed, and higher scores indicate a higher self-determined motivation for solitude. The Motivation for Solitude Scale–Short Form is a reliable and valid measure of the motivation for solitude [106].

*Working alliance* will be assessed with the Working Alliance Inventory (Working Alliance Inventory-Short Revised) [107] adapted for guided internet interventions (WAI-I) [108]. The WAI-I comprises two subscales: (1) task and goal agreement dimension and (2) bond with the guide dimension (bond). The full scale comprises 12 items (eg, “With the online program, it has become clearer to me how I can change”) that are answered on a 5-point Likert scale ranging from 1 (never) to 5 (always). Participants in the ICBT condition without guidance will only respond to the 8 items of the task and goal dimension as the items of the bond dimension are not plausibly answerable. The WAI-I is a valid instrument for measuring working alliance in the context of guided interventions and shows good internal consistency for both the total score and the 2 subscales [108].

#### Assessment of Moderators

*Mobility* will be assessed using the corresponding subscale of the Patient Questionnaire for Medical Rehabilitation (Indicators of Rehabilitation Status-3) [109]. Respondents rate 4 items on a 5-point scale about how many difficulties they experienced during the past 4 weeks (eg, climbing a staircase over 3 floors). Items are rated on a 5-point scale from 1 (*impossible*) to 5 (*no difficulties*). The mobility subscale shows good internal consistency (Cronbach α=.85) [109].

*Attachment style* will be measured using the Adult Attachment Scale (AAS) [110,111]. The AAS comprises 16 items forming three subscales: (1) comfortability with closeness and intimacy, (2) the degree to which one can depend on others when they are needed, and (3) the degree to which one is worried about being rejected or unloved. The items are rated on a 5-point scale ranging from 1 (not at all characteristic of me) to 5 (very characteristic of me). The AAS shows satisfactory internal consistency (Cronbach α=.72-.79) [110].

*Childhood trauma* will be assessed using the 28-item Childhood Trauma Questionnaire [112,113]. Respondents are asked about their experiences of sexual, physical, and emotional maltreatment and physical and emotional neglect in childhood and adolescence. Items are rated on a 5-point Likert scale ranging from 1 (never true) to 5 (very often true). Higher values indicate a higher degree of childhood maltreatment. All scales (except physical neglect) show high internal consistency (Cronbach α ≥.89) [112].

### Sample Size

A power analysis was conducted using G*Power 3 [114]. We aim to detect small effect sizes [115] of 𝑓=0.10 (equivalent to Cohen *d*=0.20) regarding the time×group interaction for the 2 active conditions at an α error level of .05. A power analysis revealed that a sample size of 80 participants in each of the active study arms is required to detect a statistically significant difference with a power (1 – β) of 0.80, assuming correlations of *r*=0.60 between before and posttreatment measures, as previously found in another trial on ICBT for loneliness [57]. Sample size was further estimated based on a dropout rate of approximately 25%. We finally decided to randomize 100 participants to each of the active conditions. For the comparisons between the active conditions and the wait-list, 50 participants were considered sufficient for the wait-list control group condition as between-group effect sizes were assumed to be large based on the results of the aforementioned Swedish trials [54,57]. Consequently, we aim to randomize 250 participants with a randomization ratio of 2:2:1.

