## Discussion

### General Discussion

Chronic loneliness is a prevalent clinical phenomenon in the population, with a variety of adverse effects on mental and physical health [8], leading to increased mortality [9]. Psychological interventions have generally been shown to be effective in reducing loneliness [48]. Such interventions at an individual level may play a crucial role in reducing the burden of loneliness and complementing social and societal-based interventions [122-124]. Although various treatments for alleviating loneliness have been developed and tested, more well-controlled clinical trials are needed to inform about efficacious interventions for loneliness.

This study aims to test the efficacy of an internet-based self-help intervention (*SOLUS-D*) in reducing loneliness. We expect participants in both intervention groups to show greater decreases in loneliness compared with a wait-list control group at the posttreatment time point. Furthermore, reductions in loneliness will be expected to be more pronounced in participants receiving guidance than in the group without guidance. By comparing the 2 intervention groups with and without guidance, we will be able to inform about the incremental effect of guidance beyond that of the ICBT intervention. We will also look at acceptability aspects such as intervention satisfaction, adherence, and potential negative effects to further refine the intervention. In addition, we will investigate potential moderating variables on an exploratory level to gain insights into how and for whom exactly the intervention works. Furthermore, knowledge on mechanisms of change in treating chronic loneliness will be expanded. This will provide further insight into the maintaining factors of chronic loneliness that interventions should focus on and, at the same time, test the proposed model of chronic loneliness [19]. Finally, the results of this study will inform which individuals can profit (most) from an internet-based ICBT intervention for loneliness.

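### The sample size calls a time×group interaction of f = 0.10 equivalent to d = 0.20; it is d = 0.40, and power for d = 0.20 is about 0.29, not 0.80

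*Protocol article*

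**What the plan says.** The Sample Size section of the protocol article gives every input to the calculation:

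- Software: "A power analysis was conducted using G*Power 3".
- Target effect: f = 0.10, described as "equivalent to Cohen *d*=0.20) regarding the time×group interaction for the 2 active conditions".
- Error rate and power: "at an α error level of .05", and "to detect a statistically significant difference with a power (1 – β) of 0.80".
- Correlation: "assuming correlations of *r*=0.60 between before and posttreatment measures".
- Result: "a sample size of 80 participants in each of the active study arms is required".

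It then assumes about 25% dropout and randomises 100 to each active arm. The 50 wait-list participants are justified separately, by large effects in earlier trials.

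The Statistical Analyses section tests differential efficacy through the condition-by-time interaction. It defines the reported effect size as the treatment effect divided by the pooled SD. The General Discussion says of the guided-versus-unguided comparison that "we will be able to inform about the incremental effect of guidance beyond that of the ICBT intervention".

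**The concern.** The equivalence d = 2f belongs to a one-way comparison of two group means. The effect sized here is a time×group interaction, where the same f stands for a larger difference between arms. If the conversion is wrong, the article claims 80% power for a guidance effect half the size of the one it can detect with that power.

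Guided versus unguided is the only comparison with a formal power calculation, and superiority of guidance is a stated hypothesis under Objectives. A reader who believes the trial had 80% power at d = 0.20 could take a non-significant result as fair evidence that guidance adds little. That reading is not supported if the real power at d = 0.20 is nearer 30%.

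**Working it through.** **Inputs (Sample Size section).** f = 0.10; α = 0.05 (the interaction F test corresponds to a two-sided test); power 0.80; ρ = 0.60; k = 2 active arms; 80 per arm. The number of time points is taken as m = 2, because the section cites one correlation between the pre- and post-treatment measures. Step 1 supports this.

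**Step 1: reproduce the plan's figure.** For the within-between interaction in repeated-measures ANOVA:

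- λ = f² × N × m / (1 − ρ), with df1 = (k − 1)(m − 1) and df2 = (N − k)(m − 1).
- With N = 160: λ = 0.01 × 160 × 2 / 0.40 = 8.0, df = 1 and 158, power = 0.803.
- The smallest N reaching 0.80 is 159, that is 80 per arm. The plan's figure is reproduced.

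Other set-ups at f = 0.10 do not match 80 per active arm:

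| Groups | Time points | Total N |
|---|---|---|
| 2 | 3 | 130 |
| 2 | 5 | 98 |
| 3 | 2 | 198 |
| 3 | 3 | 162 |

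**Step 2: convert f to d for this interaction.** Take an outcome SD of 1 and equal expected baselines, as randomisation implies. The cell means (pre, post) are (0, 0) for unguided and (0, d) for guided.

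- Grand mean d/4; group means 0 and d/2; time means 0 and d/2.
- Interaction term for guided at post: d − d/2 − d/2 + d/4 = d/4. The other three cells are also ±d/4.
- So f = √(mean of (d/4)²) = d/4.

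Hence f = 0.10 means d = 0.40, and d = 0.20 means f = 0.05.

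**Step 3: power for d = 0.20 (f = 0.05), same formula.**

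| Analysed per arm | λ | Power at d = 0.20 | Effect detectable with 80% power |
|---|---|---|---|
| 75 (100 × 0.75) | 0.0025 × 150 × 2 / 0.40 = 1.875 | 0.275 | d ≈ 0.41 |
| 80 | 0.0025 × 160 × 2 / 0.40 = 2.0 | 0.290 | d ≈ 0.40 |
| 100 (no dropout) | 0.0025 × 200 × 2 / 0.40 = 2.5 | 0.350 | d ≈ 0.36 |

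For 80% power at d = 0.20 the formula needs N = 630, or 315 analysed per arm. That is 315 / 0.75 = 420 randomised per arm at 25% dropout.

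**Step 4: check without f.**

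- SD of change = √(2 × (1 − 0.60)) = 0.894.
- SE of the difference in change at 80 per arm = 0.894 × √(2/80) = 0.141.
- d = 0.20: 0.20 / 0.141 = 1.41, power 0.29.
- d = 0.40: 0.40 / 0.141 = 2.83, power 0.81 by normal approximation.
- Simulation of the change-score test (20,000 trials per effect) gave 0.288 and 0.803.

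**Step 5: variants that might rescue the claim at d = 0.20 and 80 per arm.**

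- Comparing post scores only: 0.24.
- Baseline-adjusted analysis: 0.35 (0.33 at 75, 0.42 at 100).
- One-sided interaction test: 0.41.
- Scaling by the SD of change: f = 0.10 becomes 0.40 / 0.894 ≈ 0.45, further from 0.20.

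None comes near 0.80.

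**The case against.** The strongest reply is that the sample size itself is not miscalculated. The target is f = 0.10, and 80 per arm delivers 80% power for it. Only the parenthetical is wrong, so the 0.29 applies only to a reader who takes d = 0.20 as the target. That is correct and limits the point: the error lies in the conversion and the sensitivity it advertises. But d is the scale on which the article discusses earlier trials and plans to report its own results, so it is the figure a reader will use.

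The equivalence could be saved by expressing the interaction as half the difference in change (0.40 / 2). The article's own definition, treatment effect over pooled SD, does not support that reading.

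Three further objections stand in part:

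- The planned mixed model uses all available data, including a week-5 assessment, so two-time-point figures approximate the planned analysis. They are, however, the figures on the article's own basis.
- The baseline-adjusted powers describe an analysis the article does not state. They show that the conclusion is robust but do not belong in the corrected text.
- Nothing in the article says a null result will be read as no effect, and the General Discussion sentence is not itself wrong. The misreading is a risk, not a stated plan. Nor should it be exaggerated near d = 0.40, where the 20% miss rate is the usual design risk. At d = 0.30 and 80 per arm, power is about 0.56.

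**Conclusion.** The concern holds. For the two-arm, two-time interaction that reproduces the protocol's 80 per arm, f = 0.10 is a between-arm difference in change of d = 0.40. The stated d = 0.20 is wrong by a factor of two. Power for d = 0.20 is about 0.29 at 80 per arm, so a true effect of that size would be missed about 71% of the time.

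This rests on r = 0.60, two-sided α of 0.05, equal expected baselines, equal variances at both times, and d scaled by the SD of the outcome. The first comes from the article, the second is the usual reading of its F test, and the last follows its effect-size definition. The figures for 75 and 100 per arm bracket the stated dropout and no dropout, and the conclusion is the same at both. The wait-list comparisons were not sized on this figure and are unaffected.

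**What to change.** In the Sample Size section, delete the equivalence to d = 0.20 and replace it with text along these lines:

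> An interaction effect of f = 0.10 with two groups and two time points corresponds to a between-group difference in change of d = 0.40. With r = 0.60 and 80 analysed participants per active arm, power is 80% for d of about 0.40 and about 29% for d = 0.20.

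It would be honest to add that 25% dropout from 100 leaves 75 per arm, where the detectable effect is about d = 0.41 and power for d = 0.20 is 0.275.

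Advisable, though not required by the error: state that guided versus unguided will be interpreted through the estimated difference and its 95% CI, and that non-significance alone will not be reported as absence of an incremental effect.

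The cost is a change of wording and a less favourable statement of sensitivity. Recruitment targets, allocation and analysis stay as they are.

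### Randomising 100 per active arm covers 20% dropout, not the stated 25%: 75 completers would remain against a stated need of 80

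*Protocol article*

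**What the plan says.** All the figures stand in the Sample Size section of the protocol article.

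- The target is a small effect, f = 0.10, "regarding the time×group interaction for the 2 active conditions at an α error level of .05".
- The size is that "required to detect a statistically significant difference with a power (1 – β) of 0.80", "assuming correlations of *r*=0.60 between before and posttreatment measures". The result is given as "a sample size of 80 participants in each of the active study arms is required".
- For attrition and the number randomised to each active arm: "Sample size was further estimated based on a dropout rate of approximately 25%. We finally decided to randomize 100 participants".
- The wait-list arm of 50 is justified separately, by an expected large effect. The total is 250 at 2:2:1.

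The Statistical Analyses section plans an intention-to-treat mixed-effects analysis that uses data from all participants and handles missing values by maximum likelihood. It also plans a per-protocol analysis, restricted to people with baseline and post-treatment assessments who logged into at least four modules.

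**The concern.** A dropout allowance exists so that the required number remains after losses. Here it does not: the required number is 80, the stated loss is about 25%, and the number randomised leaves 75. The figure of 100 equals 80 × 1.25, which is what results from adding 25% of the required number instead of dividing by the fraction retained.

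The affected comparison is guided against unguided treatment, for which the sample size was built and which is the second stated objective. A reader of the article will take it that 100 per arm delivers 0.80 power with a quarter of participants lost. On a completer basis it does not, and the statement could be carried unchanged into the results report.

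**Working it through.** **Inputs, all from the Sample Size section:** α = 0.05; power 0.80; f = 0.10; r = 0.60; two active arms; 80 per arm required; dropout about 25%; 100 per arm randomised. Two measurements (before and after treatment) are taken from the wording of the correlation assumption.

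**1. Reproducing the 80.** For a group × time interaction in a repeated-measures design with two groups and m measurements, the noncentrality is λ = f² · N · m / (1 − r), with N the total in the two arms. The F test has 1 and N − 2 degrees of freedom when m = 2.

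- N = 160: λ = 0.01 × 160 × 2 / 0.40 = 8.0; power 0.803.
- N = 158 (79 per arm): λ = 7.9; power 0.798.

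So 80 per arm is reproduced exactly, and it is the smallest size that reaches 0.80. With three measurements the same formula gives 65 per arm, so the published 80 rests on two.

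**2. Dropout arithmetic.**

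- Remaining at 25% loss: 100 × 0.75 = 75.
- Needed to keep 80: 80 / 0.75 = 106.7, so 107 per arm.
- Largest loss that 100 can absorb: 1 − 80/100 = 20%.
- Adding 25% to the requirement: 80 × 1.25 = 100, which matches the plan.

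**3. Completer power at the planned size.** At 75 per arm N = 150 and λ = 0.01 × 150 × 2 / 0.40 = 7.5, which gives power 0.777. The range for a dropout of approximately 25% is:

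| Dropout | Completers of 100 | Needed to keep 80 | Completer power |
|---|---|---|---|
| 20% | 80 | 100 | 0.803 |
| 23% | 77 | 104 | 0.787 |
| 25% | 75 | 107 | 0.777 |
| 27% | 73 | 110 | 0.765 |

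**4. What the mixed model recovers.** The assumptions here are not in the documents: data missing at random, time treated as categorical, unit variance at each visit, and r = 0.60 between every pair of visits. Suppose 100 per arm have baseline and 75 have week 10.

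With complete pairs, the change score has variance 2(1 − 0.60) = 0.80, so 80 pairs give 0.80/80 = 0.0100 for the mean change in an arm. This variance splits into a part not explained by baseline, 1 − 0.60² = 0.64, and a part due to baseline, (1 − 0.60)² = 0.16. Maximum likelihood estimates the first from the 75 and the second from all 100:

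0.64/75 + 0.16/100 = 0.00853 + 0.00160 = 0.01013.

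The equivalent number of complete pairs is 0.80/0.01013 = 78.9 per arm, with power of about 0.797. If 10 of the 25 dropouts per arm also give week-5 data, the equivalent number is 80.1 (power 0.803). If all 25 do, it is 81.4 (power about 0.81).

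**The case against.** The strongest objection is that completers are not the basis of the primary analysis. The planned model uses every randomised participant, baseline is collected before randomisation, and there is a week-5 visit. This stands. Under the assumptions in step 4 the loss in the primary analysis is between nothing and about one participant-equivalent per arm. A reader might infer that only 75 per arm can be analysed at week 10, or that the primary analysis is seven participants per arm short. The Statistical Analyses section does not support either reading. The figure of 75 describes completers, and it is also the ceiling, at the stated dropout, for each active arm of the per-protocol set. The recovery does have limits: a random-slope model with linear time, or dropout that is not at random, could give other figures.

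The article also prints no inflation formula, and its wording is compatible with a pragmatic rounding. This stands too. The figure of 100 is consistent with multiplying by 1.25, but that this was done cannot be shown. The inconsistency does not depend on it, since 75 is below 80 whichever route was taken.

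The word approximately does not close the gap. Only a loss of 20% or less keeps 80, and even 23% leaves 77. Nor does the section offer the mixed model as its reason for accepting 100: it sizes the trial on before and after measures and then adds an allowance for dropout.

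**Conclusion.** The point holds as an inconsistency in stated figures. With 80 per arm required and 25% lost, 100 per arm is not enough; it corresponds to 20%. The shortfall is five completers per active arm, and completer power is 0.777 instead of 0.803. This takes f = 0.10, r = 0.60 and two measurements as given.

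The practical effect is small. In the planned likelihood-based analysis power stays at about 0.80 if data are missing at random and r = 0.60 applies between visits. The finding does not show that the trial is materially underpowered or that more participants are needed, and it does not touch the wait-list arm. The sentence should still be corrected, because readers will rely on it to judge how much attrition the design can bear.

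**What to change.** Keep 250 randomised and restate the dropout sentence in one of two ways:

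- 100 per active arm allows for 20% dropout while keeping 80 completers; or
- with 25% dropout, 75 completers per active arm remain, and completer power is about 0.78 at f = 0.10 and r = 0.60.

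With the second wording, a clause could add that the mixed model also uses the partial data of dropouts, with power of about 0.80 under the missing-at-random and correlation assumptions above.

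The cost is one restated figure, with no change to recruitment, allocation or analysis. For comparison, holding 80 completers at 25% dropout would take 107 + 107 + 54 = 268 participants at 2:2:1, which is 18 more than planned. The small loss does not call for that.
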